**Proceed**

895 **Questionnaire**

---

896

897 **Decision Aid / Fact Sheet**

898 **This set of questions relates to your experience with the resource you were assigned to review**

899 Which resource were you assigned to review?

- 900 ☐ JE decision aid website – next five questions appear
- 901 ☐ Health Direct JE fact sheet – next two questions only

902 Did you review the resource?

- 903 ☐ Yes, the whole resource
- 904 ☐ Yes, only part of it
- 905 ☐ No, I didn't review it

906 Please estimate the amount of time you spent reviewing this information (in minutes): \_\_\_\_

907 *NB: Text validation applied to ensure only whole numbers can be inputted*

908 The length of the decision aid was:

- 909 ☐ Too long
- 910 ☐ Too short
- 911 ☐ Just right

912 I found the decision aid was:

- 913 ☐ Slanted towards alternatives to vaccination
- 914 ☐ Slanted towards vaccination
- 915 ☐ Balanced

916 The amount of information was:

- 917 ☐ Too much
- 918 ☐ Too little
- 919 ☐ Just right

920 Please tell us your thoughts on the decision aid. What did you like, what didn't you like, and how can we improve it? \_\_\_\_ (free text, optional)

922 **Japanese encephalitis (JE)**

923 **This next set of questions relate to your knowledge of Japanese encephalitis.**

924 Please review each of the following statements about Japanese encephalitis (JE) and tell us if you think they are true, false, or if you're unsure:

| Statements                           | True | False | Unsure |
|--------------------------------------|------|-------|--------|
| You can catch JE from another person |      | X     |        |

|                                                                                                        |   |   |  |
|--------------------------------------------------------------------------------------------------------|---|---|--|
| JE is spread by mosquito bites                                                                         | X |   |  |
| JE can be serious: some people may die from it, and some who survive will have long-term health issues | X |   |  |
| There is a specific treatment that can help your body fight JE                                         |   | X |  |
| JE can be prevented                                                                                    | X |   |  |
| JE is caused by a bacteria                                                                             |   | X |  |
| Most travellers to JE risk areas don't get JE                                                          | X |   |  |
| Two vaccines for JE are available in Australia                                                         | X |   |  |
| Avoiding mosquito bites can lower your risk of getting JE                                              | X |   |  |

926 *NB: Correct answers are indicated with red crosses*

927 How concerned are you about getting JE on your upcoming trip?

- 928 ☐ Not at all concerned
- 929 ☐ A little concerned
- 930 ☐ Moderately concerned
- 931 ☐ Very concerned

### 932 Vaccination for Japanese encephalitis (JE)

933 **This group of questions asks you specifically about JE vaccines.**

934 How important do you think getting a JE vaccine is for your health?

- 935 ☐ Not at all important
- 936 ☐ A little important
- 937 ☐ Moderately important
- 938 ☐ Very important

939

940 How safe do you think getting a JE vaccine is for you?

- 941 ☐ Not at all safe
- 942 ☐ A little safe
- 943 ☐ Moderately safe
- 944 ☐ Very safe

945

946 Do you think most of your close family and friends would want you to get a JE vaccine?

- 947 ☐ No
- 948 ☐ Yes

949

950 Do you know where to go to get a JE vaccine for yourself?

- 951 ☐ No
- 952 ☐ Yes

953

954 Do you want to get a JE vaccine before your upcoming trip?

- 955 ☐ No, I do not want to
- 956 ☐ Yes, I do want to

- 957 ☐ I am not sure  
 958 ☐ I am already vaccinated  
 959

960 **If yes - Which vaccine option do you prefer?**

- 961 ☐ Imojev (live) vaccine  
 962 ☐ JEspect (inactivated) vaccine  
 963 ☐ I don't have strong feelings either way  
 964 ☐ I want to get vaccinated but I haven't decided which option yet

965 **Considering the option you prefer for your upcoming trip, please answer the following questions:**

|                                                                                             | Strongly Agree | Agree | Neither Agree nor Disagree | Disagree | Strongly Disagree |
|---------------------------------------------------------------------------------------------|----------------|-------|----------------------------|----------|-------------------|
| I know which options are available to me                                                    |                |       |                            |          |                   |
| I know the benefits of each option                                                          |                |       |                            |          |                   |
| I know the risks and side effects of each option                                            |                |       |                            |          |                   |
| I am clear about which benefits matter most to me                                           |                |       |                            |          |                   |
| I am clear about which risks and side effects matter most to me                             |                |       |                            |          |                   |
| I am clear about which is more important to me (the benefits or the risks and side effects) |                |       |                            |          |                   |
| I have enough support from others to make a choice                                          |                |       |                            |          |                   |
| I am choosing without pressure from others                                                  |                |       |                            |          |                   |
| I have enough advice to make a choice                                                       |                |       |                            |          |                   |

|                                           |  |  |  |  |  |
|-------------------------------------------|--|--|--|--|--|
| I am clear about the best choice for me   |  |  |  |  |  |
| I feel sure about what to choose          |  |  |  |  |  |
| This decision is easy for me to make      |  |  |  |  |  |
| I feel I have made an informed choice     |  |  |  |  |  |
| My decision shows what is important to me |  |  |  |  |  |
| I expect to stick with my decision        |  |  |  |  |  |
| I am satisfied with my decision           |  |  |  |  |  |

966

967

1009 [Questionnaire](#)

---

1010

1011 In late 2024, you were planning a trip to a JE endemic area in [pipe previous answer]. Did you take  
1012 your trip as planned?

1013 - Yes – skip to ‘please select the country you spent the most time in from the drop-down list’

1014 - No

1015 How did your plans change?

1016 - Cancelled the trip

1017 - Chose a different destination

1018 - Delayed the trip

1019 - Other (please specify)

1020 Please provide any further details about why your travel plans changed (optional). *Free text box.* –

1021 **end survey**

1022 Please review this list of countries before answering the next question:

1023 ☐ Bangladesh

1024 ☐ Bhutan

1025 ☐ Brunei Darussalem

1026 ☐ Burma (Myanmar)

1027 ☐ Cambodia

1028 ☐ China

1029 ☐ India

1030 ☐ Indonesia

1031 ☐ Japan

1032 ☐ Lao People’s Democratic Republic

1033 ☐ Malaysia

1034 ☐ Nepal

1035 ☐ North Korea

1036 ☐ Pakistan

1037 ☐ Papua New Guinea

1038 ☐ Philippines

1039 ☐ Russia

1040 ☐ Singapore

1041 ☐ South Korea

1042 ☐ Sri Lanka

1043 ☐ Taiwan

1044 ☐ Thailand

1045 ☐ Timor-Leste

1046 ☐ Vietnam

1047

1048 Since November 2024, have you travelled to any of the countries listed above?

1049 ☐ Yes

1050 ☐ No – End survey

1051

1052 Please select the country you spent the most time in from the drop-down list (required)

1053 NB: drop-down menu limited to JE-endemic areas excluding Australia  
1054

1055 Did you visit a healthcare provider to discuss your trip before travelling overseas?

1056 - Yes

1057 - No – skip to 'Did you take any measures to avoid mosquito bites'

1058 Did you receive a vaccine for Japanese encephalitis before your trip?

1059 - Yes, I received the JEspect (inactivated) vaccine

1060 - Yes, I received the Imojev (live-attenuated) vaccine

1061 - Yes, but I don't recall which JE vaccine I received

1062 - No, I did not get vaccinated – skip to 'Why did you decide not to get vaccinated'

1063 - I don't remember

1064 How many vaccine doses did you receive?

1065 - 1 dose

1066 - 2 doses (28 days apart)

1067 - 2 doses (7 days apart)

1068 - I don't remember

1069 Why did you decide to get vaccinated? (Select all that apply)

1070 - I was worried about my risk of catching JE

1071 - I was worried about the lack of treatment options for JE

1072 - I wanted to do everything I could to reduce my risk of JE

1073 - My doctor recommended that I receive the vaccine

1074 - I wasn't sure if I could avoid mosquito bites at all times

1075 - I trusted that the JE vaccine is safe

1076 - I believed that the JE vaccine would protect me

1077 - The cost of the vaccine was not a concern for me

1078 - Other, please specify

1079 Why did you decide not to get vaccinated (Select all that apply)

1080 - I wasn't worried about my risk of catching JE

1081 - The lack of treatment options didn't worry me

1082 - I didn't think the risk of JE was high enough

1083 - My doctor did not recommend the vaccine

1084 - My doctor told me I did not need the vaccine

1085 - I was confident I could avoid mosquito bites

1086 - I was worried about possible side effects

1087 - I was not sure that the vaccine would protect me

1088 - I was not able to pay the cost of the vaccine

1089 - Other, please specify

1090 Did you take any measures to avoid mosquito bites while overseas?

1091 - Yes

1092 - No

- 1093        -    Can't recall
- 1094    **If yes,** what measures did you take? (matrix-style question. Response options: frequently,  
1095 sometimes, often)
- 1096        -    Wore long-sleeved shirts and long pants outdoors
- 1097        -    Applied insect repellent (e.g. containing DEET, picaridin or OLE) to exposed skin
- 1098        -    Stayed in screened rooms or under a permethrin-treated bed net
- 1099        -    Avoided going out after dark
- 1100        -    Other, please specify
- 1101    How many times were you bitten by mosquitoes while overseas?
- 1102        -    Many times
- 1103        -    A few times
- 1104        -    Not at all
- 1105

1181

1182

1183

1184

1185

1186

1187

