### 153 **4.1. INTERVENTION ARM**

154 Participants randomised to the intervention arm will receive a link to the online Japanese  
155 encephalitis vaccine decision aid (JEVaDA) tool. This tool has been developed in accordance with  
156 International Patient Decision Aids Standards (IPDAS – Appendix 1) and designed through a  
157 comprehensive co-design and user-testing framework.

158 The JEVaDA tool features a self-guided, step-by-step approach divided into three main sections, with  
159 additional pages such as an FAQ. It provides detailed information on Japanese encephalitis, including  
160 its geographic distribution, modes of transmission, clinical features, severity and risk. It also covers  
161 preventive measures, including mosquito bite avoidance strategies and a comparison of available  
162 vaccines in Australia. Participants are encouraged to reflect on their personal circumstances and how  
163 their beliefs and values align with their intended decision, and are prompted to consult with their  
164 healthcare provider to discuss their options.

165 The tool includes visual aids and interactive elements designed to support decision-making, such as a  
166 side-by-side risk-benefit analysis graphic and a values clarification exercise. JEVaDA is intended as an  
167 educational resource and emphasises the importance of consulting with a trusted healthcare  
168 provider before making a vaccination decision.

169 A downloadable short-form PDF version of the decision aid is available on the website. This PDF  
170 version contains a condensed version of the online content and lacks the interactive features of the  
171 online tool.

The time participants spend using the decision aid will vary based on their engagement with the content. Based on pilot testing, we anticipate that most users will spend approximately 15 minutes or less with the tool.

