### **Vaccine uptake**

For participants who consent to the follow-up survey, uptake of JE vaccine will be assessed through self-reported responses to the question, "Did you receive a vaccine for Japanese encephalitis before your trip?". While this approach relies on self-reported data rather than clinical records, it is a pragmatic choice given the research team's capacity and the limitations of the Australian Immunisation Register, which does not require mandatory reporting of non-National Immunisation Program vaccines for adults. Additionally, it minimises participant burden and preserves anonymity.

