### 2.2 Missing data

All available data will be used for the analysis. Multiple imputation will be used to handle any missing data.

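### As scripted, the follow-up survey records JE vaccine uptake only for travellers who saw a healthcare provider, a step the decision aid prompts, and the SAP has no rule for those who are skipped

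*Combined protocol and SAP*

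**What the plan says.** **Who is meant to be assessed.** Protocol 5.7.2 (Vaccine uptake) reads "For participants who consent to the follow-up survey, uptake of JE vaccine will be assessed through self-reported responses to the question" on pre-trip vaccination. It sets no condition about seeing a provider. SAP Secondary Outcome 3 frames its hypothesis for adults planning travel to JE risk areas, again without that condition. SAP 1.3 analyses secondary outcomes in the ITT and modified ITT sets, and neither is restricted to people who saw a provider.

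**Who is actually asked.** In the Appendix 4 follow-up questionnaire, "Did you visit a healthcare provider to discuss your trip before travelling overseas" comes directly before "Did you receive a vaccine for Japanese encephalitis before your trip". A No to the first carries the instruction "skip to 'Did you take any measures to avoid mosquito bites". The vaccine question appears only once in that survey, so a traveller sent past it is never asked.

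**What the aid does.** Protocol 4.1 says that aid users reflect on their circumstances "and are prompted to consult with their" healthcare provider, and that the tool "emphasises the importance of consulting with a trusted healthcare" provider before deciding. Protocol 4.2 describes a service finder on the control page but no such prompt.

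**How the SAP handles the answer.** Secondary Outcome 3 codes Yes as 1, and No or not remembering as 0. It gives no value for a traveller who was never asked. SAP 2.2 says only "Multiple imputation will be used to handle any missing data".

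**A second routing problem.** Respondents whose trip went as planned jump to the country drop-down. Those whose trip did not are asked how plans changed, then "Please provide any further details about why your travel plans changed (optional"; after that box the script ends the survey. The item asking about travel to a listed country since November 2024 lies between these two paths.

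**The concern.** The outcome defined in the protocol and SAP belongs to all follow-up travellers. The outcome the script can record belongs to those who saw a provider about the trip. That visit happens after randomisation, and the intervention encourages it. Restricting to visitors therefore selects the sample on something the arm may change. If part of the aid's effect on vaccination works by sending people to a provider, a visitor-only comparison cannot show that part.

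Imputation does not repair this. Uptake is never observed in any non-visitor, so nothing in the data informs their uptake, and putting provider visit in the imputation model would not help. Any imputed value is borrowed from visitors, who are more likely to have been vaccinated.

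Uptake matters to the trial's message. It is in the protocol's hypothesis (3.1), its synopsis (1.2) and the SAP's statement of design (1.1).

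**Working it through.** **1. The plan's own figure.** The documents state no figure for uptake. The only design calculation is for the DCS (SAP 2.5): effect 0.30 SD, correlation 0.5, two-sided 0.05, 175 per group. The residual SD is √(1 − 0.5²) = 0.866, which gives power 0.8998 at 175 per group (176 needed for 90%), and 350/0.70 = 500. This reproduces to rounding and is untouched by the present point.

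**2. Tracing the script.**
- Trip as planned, provider seen: vaccine question asked.
- Trip as planned, provider not seen: vaccine question skipped.
- Trip not as planned: survey ends after the free-text box, whether the trip was cancelled, delayed or diverted.
- Item on travel since November 2024: a Yes on the planned trip jumps beyond it and a No ends before it, so nobody reaches it.

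**3. Effect on the odds ratio.** All rates below are assumptions. Let v be the proportion who visit a provider, p uptake among visitors and q uptake among non-visitors. All-traveller uptake is v·p + (1 − v)·q, and the survey records p only. With q = 0, unadjusted, aid relative to control (SAP Table 7 takes JEVaDA as reference, so its ratio would be the inverse):

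| Visits, aid / control | Uptake in visitors, aid / control | All-traveller uptake, aid / control | All-traveller OR | Visitor-only OR |
|---|---|---|---|---|
| 50% / 40% | 30% / 30% | 15% / 12% | 1.29 | 1.00 |
| 45% / 30% | 30% / 30% | 13.5% / 9% | 1.58 | 1.00 |
| 40% / 30% | 30% / 30% | 12% / 9% | 1.38 | 1.00 |
| 40% / 30% | 26.25% / 30% | 10.5% / 9% | 1.19 | 0.83 |
| 50% / 30% | 24% / 30% | 12% / 9% | 1.38 | 0.74 |
| 30% / 30% | 40% / 30% | 12% / 9% | 1.38 | 1.56 |
| 30% / 30% | 30% / 30% | 9% / 9% | 1.00 | 1.00 |

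First row: (0.15/0.85)/(0.12/0.88) = 1.29. In rows 4 and 5 the extra visitors brought in by the aid vaccinate at 15%; for row 4, (0.30 × 0.30 + 0.10 × 0.15)/0.40 = 26.25%. The visitor-only ratio can be null, reversed or too large.

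**4. Imputation.** A simulation of 200,000 travellers used visits of 40% (aid) and 30% (control) and 30% uptake among visitors, and imputed non-visitors from an arm-only logistic model fitted in visitors. It gave an OR of 0.99 with uptake of 29.7% and 29.9%. The simulated truth was an OR of 1.34 with 11.9% and 9.1%.

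**5. Absolute uptake.** If imputation ignores intention and non-visitors are in truth unvaccinated, the overstatement is 1/v: 2.5-fold at 40% visits and 2.0-fold at 50%. Rarer visits would raise it.

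Now let imputation use intention. Assume 30% intend to vaccinate; 70% of intenders and 27% of others visit (0.21 + 0.189 = 39.9%); uptake among visitors is 50% and 7.9%.
- True uptake: 0.21 × 0.50 + 0.189 × 0.079 = 12.0%.
- Added by imputing non-visitors: 0.09 × 0.50 + 0.511 × 0.079 = 8.5%, that is, 14% of the 60.1% who did not visit.
- Reported uptake: 20.5%, a 1.7-fold overstatement.

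**6. Coding non-visitors as unvaccinated.** With visits of 40% and 30%, and 30% uptake among visitors, coding them 0 gives OR 1.38. If 2% of non-visitors were in fact vaccinated, uptake is 13.2% and 10.4% and the OR is 1.31. The coding error is modest here, but it should be examined.

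**The case against.** A reader might infer that non-visitors will certainly be imputed, that the aid's effect will be erased to an OR of 1.00, and that uptake will be at least doubled. The documents do not support that much.

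- **Handling is unspecified, not settled.** SAP 2.2 is one general sentence and does not say that a survey skip counts as missing. Appendix 4 treats vaccination as given by health workers, so the skip can be read as implying no vaccine. This stands as to certainty. It does not remove the problem, because no such coding rule is written.
- **The OR of 1.00 is built into the assumption** of equal uptake among visitors. No visit rates are given, and Protocol 4.1 shows a prompt, not an effect on visits. If neither visits nor uptake among visitors differ by arm, a null stays null. This stands: the direction of bias is not fixed.
- **The illustrations are not the planned model.** Secondary Outcome 3 adjusts for post-intervention intention, age and sex, and imputation using intention reduces the overstatement. This stands, and is why the lower figure is 1.7. Bias remains in that example.
- **Absolute uptake has no planned table**; Table 7 reports adjusted odds ratios. True, but a reported uptake percentage would carry the error.
- **Coding every skipped traveller 0 has its own error.** It misclassifies anyone vaccinated without a trip-specific visit, including those who said in the pre- or post-intervention survey that they were already vaccinated. This stands and shapes the fix.
- **The unreachable item may be a misplaced instruction**, and the live REDCap build is not shown. Ending the survey for cancelled trips also fits a pre-travel outcome. What stands is the loss, as scripted, of delayed and diverted travellers.

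**Conclusion.** The concern holds for the questionnaire as written. Uptake is recorded only for travellers who visited a provider about the trip, against the population stated in Protocol 5.7.2 and SAP Secondary Outcome 3, and the SAP does not say how the rest are coded. Visitor-only analysis or imputation from visitors can bias the uptake odds ratio either way, depending on how the aid changes visits and on uptake among the extra visitors. Absolute uptake would be overstated about 1.7 to 2.5-fold, given assumed visit rates of 40 to 50% and non-visitors who are in truth unvaccinated; these are illustrations, not bounds. The separate routing defect loses travellers who delayed or switched to another JE-risk country.

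This is a should-fix point. Uptake is the third secondary outcome, self-reported in an optional survey. The DCS is measured before and immediately after the materials, so the primary analysis and its sample size are not affected.

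**What to change.** **If the follow-up survey can still be changed:** ask the vaccine question of every follow-up traveller by removing the skip or placing the question above the provider item. Route respondents whose plans changed to the item on travel since November 2024. The cost is a REDCap branching edit and a few seconds per respondent.

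**If it has already run**, which the trip dates offered in Appendix 4 and the SAP version dates make likely:
- State in SAP Secondary Outcome 3 that respondents skipped for no provider visit are coded not vaccinated and are not imputed.
- Except those who reported being already vaccinated in the pre- or post-intervention survey, and give a stated rule for them.
- Add a sensitivity analysis that varies uptake among non-visitors.
- Report provider visits by arm.
- Check the live REDCap routing against the script, and report how many follow-up respondents exited because their plans changed.

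This costs a short dated SAP amendment and one extra table. The travellers lost by the early exit cannot be recovered, so report that as a limitation.

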## Section 1: General information

### 1.1 Study design

This is a single-blinded randomised controlled trial (RCT) evaluating the impact of a web-based Japanese encephalitis vaccine decision aid (JEVaDA) on informed vaccine decision-making and vaccine uptake among Australian travellers, compared to a government-funded online information sheet (HealthDirect). Participants are not blinded to allocation, but investigators are.

